#### Outcomes

The primary objectives of this study are to describe how implementation strategies affect the implementation of PrEP care in FP clinics, by analyzing clinic study data over time from pre- to post-PrEP implementation (Table 1), and to describe the PrEP cascade among women seeking care in FP clinics in Metro Atlanta (Table 2). The outcomes within the PrEP cascade include HIV testing, risk assessment, and prevention counseling inclusive of PrEP; PrEP prescriptions; and PrEP uptake, persistence, and adherence in PrEP-eligible women (Figure 2). As data capturing the entire span of the PrEP cascade and factors impacting successful implementation could not be captured by one data source, multiple data sources were necessary.

**Table 1 table1:** Description of outcomes supporting the study’s primary objective to describe how implementation strategies affect the implementation of HIV pre-exposure prophylaxis care in family planning clinics among women aged 13 to 45 years.

Outcomes		Definitions
**Clinic staff (survey, focus groups, and key informant interviews)**		
	Implementation processes	Degree of adherence to the clinic-specific PrEP^a^ implementation plans over assessment period
	Factors affecting implementation	CFIR^b^-guided factors, assessed after PrEP implementation begins, that contribute to adherence to or deviations from the clinic-specific PrEP implementation plans
**Clinic chart abstraction**		
	HIV testing	Change over time from pre- to post-PrEP implementation in the percentage of visits at the clinic in women aged 13 to 45 years where HIV testing was performed
	HIV risk assessments	Change over time from pre- to post-PrEP implementation in the percentage of visits at the clinic in women aged 13 to 45 years with a documented HIV risk assessment
	PrEP prescriptions	Change over time from pre- to post-PrEP implementation in the percentage of visits at the clinic in women aged 13 to 45 years at which a prescription for PrEP was received
**Clinic patients (exit survey)**		
	HIV prevention counseling	Change over time from pre- to post-PrEP implementation in the percentage of clinic patient participants who report whether they received HIV prevention counseling during their visit to the clinic that day
	HIV prevention counseling inclusive of information about PrEP	Change over time from pre- to post-PrEP implementation in the percentage of clinic patient participants who receive HIV prevention counseling that includes information about PrEP during their visit to the clinic that day

^a^PrEP: pre-exposure prophylaxis.

^b^CFIR: Consolidated Framework for Implementation Research.

**Table 2 table2:** Description of outcomes supporting the study’s primary objective to describe the HIV pre-exposure prophylaxis care cascade among women aged 13 to 45 years.

Outcomes		Definitions
**Clinic chart abstraction**		
	HIV testing	Percentage of visits at the clinic in women aged 13 to 45 years where HIV testing was performed
	HIV risk assessments	Percentage of visits at the clinic in women aged 13 to 45 years with a documented HIV risk assessment
	PrEP^a^ prescriptions	Percentage of visits at the clinic in women aged 13 to 45 years at which a prescription for PrEP was received
**Clinic patients (exit survey)**		
	HIV prevention counseling	Percentage of clinic patient participants who report whether they received HIV prevention counseling during their visit to the clinic that day
	HIV prevention counseling inclusive of information about PrEP	Percentage of clinic patient participants who receive HIV prevention counseling that includes information about PrEP during their visit to the clinic that day
**Cohort patients**		
	PrEP uptake	Participant who receives a PrEP prescription at the baseline visit, fills their prescription, and self-reports initiating PrEP
	PrEP persistence	Participant who attends at least one follow-up visit and has a documented pharmacy refill of PrEP medication at least once during each 3-month interval
	PrEP adherence—hair sample	Average tenofovir concentration measured using a small hair sample (ng/mg); percentage of participants with adherence level consistent with 7 doses per week (≥0.0370 ng/mg) [34,35]
	PrEP adherence—blood sample	Percentage of participants with dried blood spot tenofovir concentration≥1250 fmol/punch
	PrEP adherence—urine sample	Percentage of participants with tenofovir detected by urine immunoassay
	PrEP adherence—self-report	Percentage of participants reporting no missed doses in the past 7 days; percentage of participants reporting very good or excellent adherence (5 or 6 on a 6-level Likert scale) [36] in the past 30 days; percentage of participants who self-report adherence of 90% or higher
	PrEP adherence—pharmacy fill	Percentage of participants with 80% adherence by medication possession ratio defined as the number of dispensed pills divided by the number of days since starting PrEP [37,38]

^a^PrEP: pre-exposure prophylaxis.

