### Quantitative Data Analysis

#### Sample Size

The prospective cohort study will attempt to enroll up to 300 PrEP-eligible women across three clinics. Sample sizes pertaining to clinic staff and clinic patient participants were not chosen to yield a specified level of statistical power for hypothesis testing or to provide a specific level of precision for estimation of a target estimand. However, based on a sample size of 300, the study will provide the ability to estimate the percentage of PrEP-eligible women who are willing to initiate PrEP at baseline within a margin of error of approximately 4.5% (assuming a true uptake percentage of 20%). If instead only 150 participants are enrolled, the margin of error increases to 6.4%. If the actual uptake is lower than assumed, the margin of error will be less than stated.

As this is the first study of its kind focusing on the components of the PrEP cascade in this population and estimates for uptake of PrEP are not available for women seeking care in FP clinics in the Southern United States, the distribution of patients who achieve each step of the PrEP cascade is not well understood. As a result, the quantitative data analysis objectives for the study are not powered for any specific hypothesis testing aim or to achieve a particular level of precision for a specific target estimand. However, based on a sample size of 300, the study will provide 70% power or more to detect a 12% difference in PrEP uptake between race groups (binary) provided the sample size distribution between the two race groups is not more imbalanced than 2:1, assuming a true uptake percentage in two groups of 15% and 27%, and based on a 5% significance level for the test.

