#### Statistical Analysis

For quantitative outcomes defined based on chart abstraction (HIV testing, HIV risk assessments, and PrEP prescriptions) and clinic patient exit surveys (HIV prevention counseling, HIV prevention counseling including information about PrEP), we will compute the proportion of patients meeting the outcome definition (eg, portion who received an HIV test) along with 95% confidence intervals. For analyses based on clinic patient exit surveys, data from all exit surveys will be included in the statistical analysis.

For quantitative outcomes defined for cohort patients, all data will be included in analyses for all patients from enrollment until completion of the study or until the patient discontinues participation or becomes lost to follow-up. For the PrEP uptake and PrEP persistence outcomes, the proportion of patients meeting the outcome definition along with 95% confidence intervals will be computed. Association analyses will be performed using mixed logistic regression models to determine whether outcomes are associated with patient-level characteristics such as age, race, education level, and relationship status.

For PrEP adherence outcomes, data from all patients who initiate PrEP at their baseline visit will be included in the analyses. The proportion of patients meeting each PrEP adherence outcome definition along with 95% confidence intervals will be computed at the 3- and 6-month post baseline time points. Analyses will be performed using mixed logistic regression models to determine whether adherence outcomes are associated with patient-level characteristics such as age, race, education level, and relationship status and whether adherence rates change over the 6-month observation period. Analyses will be performed that also incorporate data from patients who initiate PrEP after their baseline visit. Agreement between the different PrEP adherence outcome measures will also be assessed using standard methods (eg, weighted kappa statistic).

Before the analysis of quantitative data, a comprehensive statistical analysis plan will be developed and finalized. Primary and secondary study outcomes and statistical analysis methods will be described in full detail in the study’s statistical analysis plan. This plan will be accessible on ClinicalTrials.gov once available.

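### The pharmacy-fill possession ratio accumulates from PrEP start, so the planned 3- to 6-month test of change sees only half of any shift and misses partial declines and recoveries

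*Protocol article*

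**What the plan says.** In the protocol article, Table 2 (cohort patients, pharmacy-fill row) gives one definition: "Percentage of participants with 80% adherence by medication possession ratio", the ratio being the "medication possession ratio defined as the number of dispensed pills divided by the number of days since starting PrEP". The denominator therefore always begins at PrEP start. No visit-specific window is given.

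The Statistical Analysis section says that the proportion meeting each adherence outcome "will be computed at the 3- and 6-month post baseline time points". Mixed logistic regression is then to show "whether adherence rates change over the 6-month observation period". The analysis set is stated as follows: "data from all patients who initiate PrEP at their baseline visit will be included in the analyses". Women who start later enter additional analyses. Agreement between the adherence measures is also to be assessed, with weighted kappa as the example.

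In the same table, persistence is defined by interval: besides attending a follow-up visit, a woman qualifies if she "has a documented pharmacy refill of PrEP medication at least once during each 3-month interval". Two of the self-report adherence items look back 7 and 30 days, and the hair, blood-spot and urine measures come from samples.

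**The concern.** A test of change compares adherence early with adherence late. Here the late value is an average over both periods, and about half of its window has already been scored at the early visit. A fall or rise after month 3 is diluted by the first three months before the 80% cut-off is applied. Some women whose possession in months 4 to 6 is below 80% are still counted as adherent at month 6, and some who recovered fully are still counted as non-adherent.

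Two planned results are affected: the estimate and test of change in pharmacy-fill adherence, and the month-6 agreement between this measure and those that look back days or weeks. In the second, part of any disagreement would come from the different windows and not from measurement error. The overlap is separate from how late-dispensed pills are credited. It would remain if every pill were counted only on the days it covered.

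**Working it through.** The plan gives no power or precision figure for the change test, so there is none to reproduce.

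**Inputs from the article.** Ratio = pills dispensed / days since PrEP start; cut-off 80%, read as at least 0.80; visits at 3 and 6 months.

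**Assumptions.** Start at baseline, one pill per day, visits at days 90 and 180. Fill size is not given; 30-pill fills are used where marked.

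**Algebra.** Let m1 and m2 be pills dispensed per day in days 1–90 and 91–180.
- Month-3 ratio = m1.
- Month-6 ratio = (90·m1 + 90·m2)/180 = (m1 + m2)/2.
- Observed change = (m1 + m2)/2 − m1 = (m2 − m1)/2, half of the true change between intervals.
- Adherent at month 6 if (m1 + m2)/2 ≥ 0.80, that is, m2 ≥ 1.6 − m1.

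**Hidden declines.** A woman adherent at month 3 with m2 below 0.80 is still counted as adherent when 1.6 − m1 ≤ m2 < 0.80.

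| m1 | m2 needed to pass at month 6 | Hidden range of m2 | Month-6 ratio if refills stop (m1/2) |
|---|---|---|---|
| 0.80 | 0.80 | none | 0.40 |
| 0.90 | 0.70 | 0.70–0.79 | 0.45 |
| 1.00 | 0.60 | 0.60–0.79 | 0.50 |

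If m1 exceeds 1, the surplus m1 − 1 should count as stock for the second interval. Second-interval possession is then m1 − 1 + m2, which is below 0.80 when m2 < 1.8 − m1. The hidden range is 1.6 − m1 ≤ m2 < 1.8 − m1, still 0.20 wide.

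**Hidden recoveries.** With m1 = 0.50 and m2 = 1.0 the month-6 ratio is 0.75, non-adherent. Any m1 below 0.60 would need m2 above 1.0 to pass.

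**With 30-pill fills, three by day 90 (month-3 ratio 90/90 = 1.0):**
- No later fill: 90/180 = 0.50, detected.
- One later fill: 120/180 = 0.67, detected.
- Two later fills: 150/180 = 0.83, counted as adherent, although second-interval possession is 60/90 = 0.67.

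**Complete stop.** This is hidden only if m1/2 ≥ 0.80, so m1 ≥ 1.6, or at least 1.6 × 90 = 144 pills by day 90.

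**Illustration of the effect on the test.** The article's cohort of 300 and assumed 20% uptake give 300 × 0.20 = 60 initiators. A simulation drew m1 uniformly from 0.5 to 1.25, capped at 1 (about 60% adherent at month 3). It let 30% of women move to a lower range of m2, held the others constant, and used an exact McNemar test in place of the mixed logistic model.

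| m2 in women who decline | Month-6 adherent, cumulative / interval | Power, cumulative / interval |
|---|---|---|
| 0–0.4 | 42% / 42% | 97% / 97% |
| 0.4–0.8 | 49% / 42% | 67% / 97% |
| 0.6–0.8 | 56% / 42% | 3% / 97% |

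The decline, the m1 distribution and the stability of the other women are assumptions, so only the contrast between columns is informative. The cut-offs in the first table follow from the stated definition.

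**The case against.** A reader might infer that the planned test cannot see women whose refills fall off after month 3. The documents do not support that. A woman who stops refilling drops to about 0.40–0.50 under ordinary supply, is reclassified as non-adherent and contributes to the test. She also fails persistence, which needs a refill in each 3-month interval.

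A reader might also build a dramatic case: every woman goes from 95% to 65%, the cumulative ratio is exactly 80%, and all appear adherent at both visits. That sits on the cut-off. At 94% then 65% the ratio is 79.5%, and the planned measure falls from 100% to 0%, as the interval measure does. Such a case does not estimate impact.

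Other fair points are that the hidden range is narrow and vanishes at m1 = 0.80, that pharmacy fill is one of five sources of adherence data, and that the Sample Size section says the quantitative objectives are not powered for a specific test. On agreement, the 90%-or-higher self-report item has no stated recall period and hair has no stated look-back. An interval ratio of about 90 days would still not match the 7-day and 30-day items.

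All of this limits the size of the problem without removing it. Persistence needs only one refill per interval, so the woman with three 30-pill fills and then two meets its refill condition and also passes the cumulative ratio. Neither pharmacy outcome flags her second-interval possession of 0.67. Nor is this a detail left to the analysis plan. That plan is not shown and could refine the windows, but the article states the denominator, and a plan that follows it inherits the overlap.

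**Conclusion.** The concern holds as one of attenuation. The cumulative ratio halves any change between the two intervals. At the 80% cut-off it hides second-interval possession of 0.60–0.79 after full possession in the first interval, a narrower range for lower m1, and none at m1 = 0.80. It also misses recoveries such as 50% then 100%. Complete discontinuation of refills is detected unless at least 144 pills were dispensed by day 90.

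These limits rest on equal 90-day halves, one pill per day, PrEP start at baseline and the cut-off read as at least 80%. How many women fall in the hidden range cannot be known from the article. The effect is confined to the change-over-time and agreement analyses of one adherence measure. It is a modest point that is worth correcting because the correction is cheap.

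**What to change.** In Table 2 and the Statistical Analysis section, define the possession ratio per visit interval: PrEP start to the 3-month visit, and the 3-month to the 6-month visit. Carry unused supply into the second interval and keep the 80% cut-off, stated as at least 80%. Use these interval values in the change-over-time model.

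Use the second-interval value in the month-6 agreement analysis too, and note that this reduces but does not remove the mismatch with the 7-day and 30-day items. Retain the cumulative 6-month ratio as a descriptive summary.

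The cost is a change of wording and slightly more data handling from the same dispensing dates and pill counts. No new data are needed.

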#### Cohort Patients

Data relevant to cohort patient participants will encompass medical chart review, interviewer-administered surveys, audio computer-assisted self-interviews, and pharmacologic and laboratory data. Data for cohort patient participants will be collected by trained study staff at the baseline, 3-month, and 6-month follow-up visits, with the allowance for interim visits as needed.

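### The pharmacy-fill ratio counts pills meant for days after the assessment, so a woman with weeks uncovered who refills just before it can be classed as 80% adherent.

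*Protocol article*

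**What the plan says.** The last row of the cohort section of Table 2 (Protocol article, Outcomes) gives the pharmacy-fill measure as "Percentage of participants with 80% adherence by medication possession ratio", and specifies a "medication possession ratio defined as the number of dispensed pills divided by the number of days since starting PrEP". The row states no rule for the most recent fill and no truncation of supply that runs past the assessment.

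The Statistical Analysis section says that, for adherence, "data from all patients who initiate PrEP at their baseline visit will be included in the analyses", and that the proportions meeting each adherence definition "will be computed at the 3- and 6-month post baseline time points". For this group, days since starting PrEP are therefore about the same as days since baseline. The same section enters the adherence outcomes into models of patient characteristics and of change over 6 months, and plans an analysis of agreement between the adherence measures.

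Two other statements bear on refill timing. Under Data Collection, cohort data come from "baseline, 3-month, and 6-month follow-up visits, with the allowance for interim visits as needed". The persistence row of Table 2 asks that a woman attend at least one follow-up visit and that she "has a documented pharmacy refill of PrEP medication at least once during each 3-month interval". That refill may fall anywhere in the interval, including its last day.

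**The concern.** The numerator and the denominator cover different periods. Pills handed out on day 88 mostly serve days after day 90, yet the day-90 ratio counts all of them against the 90 days already past. A woman who ran out, went without, and refilled shortly before the assessment looks the same as one who was never without pills.

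The measure is one of the outcomes listed in Table 2 in support of a primary objective. A woman passed on the strength of a late refill counts in the reported proportion, in the models and in the agreement analysis. If her drug level or self-report points the other way, part of that disagreement comes from the formula and not from her behaviour.

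**Working it through.** No figure in the document rests on this ratio, so there is none to reproduce. The check applies the printed definition to example refill histories and compares it with the days on which pills were in hand.

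**Inputs from the document.** Ratio and 80% cut-off: Table 2. Assessment at 3 and 6 months: Statistical Analysis, taken here as T = 90 and T = 180 days. One pill a day: the Introduction describes PrEP as a daily oral regimen.

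**Assumed inputs.** Pills per fill (30, 60 or 90) and the days of each fill. Neither is in the document.

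**Formulas.**
- Ratio as written = pills dispensed up to and including day T, divided by T.
- Days covered = number of days from 0 to T − 1 with pills in hand, early refills carried forward, divided by T.

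The cut-off is read as at least 80%: 0.80 × 90 = 72 pills by day 90 and 0.80 × 180 = 144 pills by day 180.

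| Assumed fills (days) | T | Ratio as written | Days covered | Days without pills |
|---|---|---|---|---|
| 30 pills: 0, 45, 88 | 90 | 90/90 = 100% | (30+30+2)/90 = 62/90 = 68.9% | 28 |
| 30 pills: 0, 50, 90 | 90 | 90/90 = 100% | (30+30+0)/90 = 60/90 = 66.7% | 30 |
| 30 pills: 0, 30, 60, 120, 179 | 180 | 150/180 = 83.3% | (90+30+1)/180 = 121/180 = 67.2% | 59 |
| 60 pills: 0, 60, 180 | 180 | 180/180 = 100% | 120/180 = 66.7% | 60 |
| 90 pills: 0, 173 | 180 | 180/180 = 100% | (90+7)/180 = 97/180 = 53.9% | 83 |

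All five histories pass at 80% as written and fail on days covered.

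**Histories where the two agree.** 30-pill fills on days 0 and 30, with none later, give 60/90 = 66.7% on both at day 90: a gap without a late refill fails either way. One 90-pill fill on day 0 gives 90/90 = 100% on both at day 90.

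**Direction.** Each covered day uses one dispensed pill, so days covered cannot exceed pills dispensed. The ratio as written is therefore never below the proportion of days covered, and the error cannot run downward.

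**Would dropping a fill on the assessment day be enough?** It repairs the second row (60/90 = 66.7%) and the fourth (120/180 = 66.7%). It leaves the first, third and fifth unchanged at 100%, 83.3% and 100%, because their last fill came 1 to 7 days before the assessment.

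**Is the pattern compatible with the plan's own persistence rule?** Take assumed 60-pill fills on days 0, 89 and 179, which meet the refill part of that rule. At day 90 the ratio is 120/90 = 133% and days covered are (60+1)/90 = 67.8%. At day 180 the ratio is 180/180 = 100% and days covered are (60+60+1)/180 = 67.2%.

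**The case against.** The strongest reply is that this is one table cell in a condensed article. The article defers full outcome definitions and methods to a statistical analysis plan, and the handling of the last fill is the kind of detail such a plan settles. That plan is not at hand and may deal with it. But the numerator, denominator and threshold are already printed in Table 2, and the narrowest added rule, ignoring a fill on the assessment day, leaves three of the five examples misclassified.

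A second reply is that a possession ratio does not claim to measure days covered, and that the definition is cited. It is fair that the two are different measures and that comparability with the cited studies has value. The row nevertheless uses the ratio to call a woman adherent over the elapsed period, and supply for later days says nothing about that period.

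Third, the consequence is limited, and this stands. Pharmacy fill is one of five sources of adherence data, beside hair, blood, urine and self-report. The article says the study is not powered for a specific hypothesis test, and no sample size rests on this ratio.

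A reader might infer more than the document supports, in three ways:
- That refills cluster around the 3- and 6-month visits, so the reported proportions must be inflated. The article describes those visits as data collection by study staff and does not say that pills are dispensed or refills timed there. Clustering is an assumption.
- That a 90-pill first fill makes the 3-month value uninformative because of this formula. Days covered gives the same 100%, so that limit comes from the size of the fill.
- That ratios above 100% distort the outcome. The outcome is pass or fail at 80%, so a value above 100% changes no classification by itself.

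**Conclusion.** The concern holds in a limited form. As printed, the definition can class a woman as at least 80% adherent when she had pills on only 54% to 69% of the days, in the histories tabulated above, because a refill at or shortly before the assessment is credited to days already past. This occurs with each assumed fill size of 30, 60 and 90 pills. The misclassification runs only upward and only for women with a late refill; a gap without one is still classed correctly.

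The examples rest on assumed fill sizes and dates. Since those and the share of women affected are not in the document, neither the bias in the 3- and 6-month percentages nor its effect on the change and agreement analyses can be sized. It is worth correcting before analysis because the direction is known and the repair is cheap.

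**What to change.** In the pharmacy-fill row of Table 2, and in the statistical analysis plan, count only supply that can cover days up to the assessment date: carry early refills forward, truncate supply at the assessment date, and divide the days covered by the days since starting PrEP. Apply the 80% cut-off to this proportion of days covered. Report the ratio as now written as a secondary figure, for comparison with the cited studies.

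The cost is a change of wording. Pill counts are already needed for the ratio and refill dates for the persistence outcome, so the same pharmacy data serve. The main measure becomes slightly less comparable with the cited definition, which the secondary figure covers. Days covered still measures possession and not ingestion, so it does not replace the drug-level measures.
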